### 2.8. Statistical Analysis

#### 2.8.1. Data Analysis Plan

All statistical analyses will be performed using IBM SPSS Statistics (version 29) and R (version 4.3, R Core Team, 2024). All tests will be two-tailed, with statistical significance set at *p* ≤ 0.05. Descriptive statistics (means, standard deviations, frequencies, and percentages, as appropriate) will be reported for all sociodemographic, clinical, and outcome variables at each assessment time point.

Analyses will follow the intention-to-treat (ITT) principle, including all randomized participants in the groups to which they were originally allocated, regardless of intervention adherence or study completion. As a sensitivity analysis, a per-protocol analysis will also be conducted including only participants who attended ≥ 80% of scheduled sessions and completed all assessment time points.

The primary analysis will be conducted using likelihood-based estimation within the cLDA framework, which incorporates all available observations under the missing-at-random (MAR) assumption. Missing data patterns, including Little’s MCAR test, will be explored descriptively but will not determine the primary analytical approach. Multiple imputation by chained equations (MICE) will be performed as a pre-specified sensitivity analysis to evaluate the robustness of the primary findings.

The primary analysis will use linear mixed-effects models (LMM) treating all three assessment time points (T0, T1, T2) as repeated observations of the outcome variable, following a constrained longitudinal data analysis (cLDA) framework. In accordance with the cLDA approach, baseline means are constrained to be equal across randomized groups, reflecting the randomization assumption while modelling T0 as the first repeated outcome. The model will include the following fixed effects: group (four levels: Control, EX, EXVERB, EXVERBPSY), time (three levels: T0, T1, T2), and their interaction (group × time). Participant will be included as a random effect (random intercept). The primary inferential interest is placed on the group × time interaction, evaluated at T1 (post-intervention, Week 18) and T2 (follow-up, Week 44). The cLDA model is robust to missing data under the missing-at-random (MAR) assumption and does not require sphericity. As a pre-specified sensitivity analysis, an ANCOVA model including baseline values as covariates will also be performed for T1 and T2 to evaluate the robustness of the primary cLDA findings [81]. The within-participant covariance of repeated measurements will be modelled using an unstructured covariance matrix. Model assumptions will be verified through inspection of residual plots, Q-Q plots, and formal tests of normality (Shapiro–Wilk) and homoscedasticity (Levene) applied to model residuals. If distributional assumptions are substantially violated, non-parametric alternatives (Friedman test for within-group comparisons; Mann–Whitney U test for between-group comparisons at each time point) will be used as sensitivity analyses, with results from both approaches reported.

For the planned comparisons and multiplicity controls, when a significant group × time interaction is found for the primary endpoint (α = 0.05, unadjusted), the following five pre-specified pairwise contrasts will be conducted simultaneously within a single testing family, with sequential Holm–Bonferroni correction applied across all five contrasts at each time point [82]: EXVERBPSY vs. Control at T1; EXVERB vs. Control at T1; EX vs. Control at T1; EXVERBPSY vs. EXVERB at T1 and EXVERB vs. EX at T1. Contrasts 1–3 evaluate the superiority of each active intervention arm over the educational control, directly addressing H1. Contrasts 4–5 evaluate the incremental contribution of each sequentially added component—PSY support and PFM activation instructions, respectively—consistent with the additive design of the trial. The same family of five contrasts will be repeated at T2 to evaluate the persistence of effects at the 6-month follow-up, addressing H3. Between-group effect sizes will be reported as Cohen’s d with 95% confidence intervals for each planned pairwise contrast, and as partial eta-squared (η^2^p) with 95% confidence intervals for the overall group × time interaction F-test. The same family of planned pairwise comparisons will also be applied to secondary outcomes. For each outcome analysed, sequential Holm–Bonferroni correction will be applied across the five pre-specified pairwise contrasts at each time point to control the family-wise error rate within that outcome [82].

To formally evaluate the dose–response pattern hypothesized in H2, a pre-specified linear trend analysis will be conducted using orthogonal polynomial contrasts applied to the group factor within the LMM framework. The four groups will be assigned contrast weights reflecting the sequential addition of intervention components and their expected incremental dose: Control = −3, EX = −1, EXVERB = +1, EXVERBPSY = +3. These weights correspond to the standard orthogonal polynomial contrast coefficients for four equally spaced ordered groups [40]. This analysis therefore assumes equally spaced incremental treatment effects across the four study arms and is intended to test the prespecified hypothesis of a monotonic additive dose–response trend, rather than implying that the additional intervention components are biologically or clinically equivalent. A statistically significant positive linear contrast at T1 will be interpreted as confirmatory evidence supporting a monotonic dose–response relationship across the additive intervention arms, consistent with H2. Results at T2 will be interpreted as exploratory, addressing the persistence of the dose–response pattern at follow-up. The effect size for the linear trend will be reported as r^2^contrast = Fcontrast/(Fcontrast + dferror). This analysis will be conducted for the primary endpoint and, as exploratory analyses, for the pre-specified secondary outcomes.

All secondary and exploratory outcomes will be analysed using the same LMM framework. Sequential Holm–Bonferroni correction will be applied across the five pre-specified pairwise contrasts for each secondary outcome, consistent with the primary analysis. However, no global family-wise error rate correction will be applied across secondary outcomes. Results will be presented with adjusted *p*-values for the planes pairwise comparisons, Cohen’s d effect sizes with 95% confidence intervals, and η^2^p for global F-tests. Findings from the prespecified secondary outcomes will be interpreted as supportive rather than confirmatory, whereas exploratory outcomes will be interpreted as hypothesis-generating.

To address H4, pre-specified exploratory association analyses will be conducted within the intervention groups combined (EX, EXVERB, and EXVERBPSY; *n* ≈ 90). To reduce potential regression-to-the-mean bias, baseline-adjusted residualised change scores will be used instead of raw change scores. Residualised change scores will be obtained as the residuals from linear regression models in which each post-intervention (T1) or follow-up (T2) value is regressed on its corresponding baseline (T0) value. Separate residualised change scores will therefore be adjusted for the T1 (post-intervention) and T2 (follow-up) assessments, each adjusted for its corresponding baseline (T0) value. For the Short FES-I, lower scores indicate improvement; therefore, more negative residualised values will reflect greater reductions in fear of falling.

Three sequential analyses will be performed: (1) Pearson or Spearman correlations between residualised psychological change scores and intervention adherence (percentage of sessions attended); (2) correlations between residualised psychological change scores and residualised change scores in the primary endpoint (Δmaximal voluntary contraction pressure assessed by manometric perineometry) and prespecified secondary outcomes at T1 and T2; and (3) hierarchical multiple regression analyses conducted within the intervention groups, in which group allocation (EX, EXVERB, EXVERBPSY) is entered in Step 1 and residualised psychological change scores are added in Step 2, with residualised change in the primary endpoint and, separately, each secondary outcome entered as the dependent variable. The increment in R^2^ (ΔR^2^) will be reported as the indicator of additional variance explained beyond group assignment.

All H4 analyses are designated as exploratory and hypothesis-generating. No adjustment for multiple comparisons will be applied, and findings will be interpreted cautiously with emphasis on effect estimates, 95% confidence intervals, and the consistency of observed associations rather than on statistical significance alone. These analyses do not constitute a formal mediation analysis and do not permit causal inference about psychological mechanisms.

In addition, pre-specified exploratory subgroup analyses will examine whether intervention effects on PFM function and UI symptom severity (ICIQ-SF) differ according to UI subtype (stress, urgency, or mixed), classified prior to randomization as described in Section 2.3. Subgroup analyses will be conducted by adding a three-way interaction term (group × time × UI subtype) to the primary LMM. Given the substantially reduced statistical power within each subtype subgroup, results will be interpreted as hypothesis-generating rather than confirmatory, and no family-wise error rate correction will be applied.

Effect sizes will be reported using partial eta squared (η^2^p) for global F-tests, Cohen’s d for pairwise between-group comparisons at each time point, and Cohen’s d with 95% confidence intervals for pre-to-post change scores within groups. Effect sizes will be interpreted using conventional benchmarks (small: d = 0.20; medium: d = 0.50; large: d = 0.80).

In addition to statistical significance, the clinical relevance of intervention effects will be evaluated using established MCIDs where available. Specifically, the ICIQ-SF will be interpreted using its published MCID (2.52 points) [83]. Four outcomes without well-established MCIDs in community-dwelling older women, including the TUG [84] and the Short FES-I, clinical relevance will be interpreted using effect sizes, 95% confidence intervals, and comparison with previously published intervention studies [85].

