### 2.6. Interventions

The intervention will consist of 36 supervised multicomponent exercise sessions, and, for one study arm, six structured PSY sessions delivered over 18 weeks. Exercise sessions will be conducted twice weekly on non-consecutive days (55–60 min/session) and will target balance, power, strength, aerobic capacity, agility/coordination, and flexibility with progressive intensity. Sessions will be led by a physiotherapist specialized in geriatrics (five years of experience), with methodological oversight by a research supervisor using a standardized supervision checklist to ensure fidelity and safety.

Participants will be allocated to one of the four groups:-G1: (EX) PMT only.-G2: (EXVERB) EX plus verbal cues to facilitate PFM contractions during balance and strength exercises.-G3: (EXVERBPSY) EXVERB plus six structured PSY sessions delivered during the intervention period.-G4: (Control Group) Participants will receive four educational sessions (one per month, 45–60 min per session) focused on the prevention of geriatric syndromes and instructions to maintain their usual physical activity. The sessions will address topics related to breathing control, postural control, balance and fall prevention, and pelvic floor (PF) health. After study completion, control participants will be offered the opportunity to receive the intervention components not undertaken during the initial study phase.

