#### 2.6.1. Adherence and Intervention Fidelity

Adherence will be promoted through regular participant contact (telephone and/or in person), flexible scheduling, and reminder messages prior to assessments. Attendance of ≥80% of scheduled sessions will be considered adequate adherence. Attendance, progression variables (e.g., elastic-band resistance and grip width), and any adverse events (AE) will be recorded throughout the intervention. Reasons for discontinuation will be documented, and outcome data will be collected at each assessment time point whenever feasible, in accordance with the intention-to-treat principle.

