#### 2.7.3. Adherence, Safety and Co-Interventions

Before each assessment session, participants will be screened for any new medical conditions or contraindications that could compromise the safe performance of the assessments. Maximal jump tests (CMJ and ABK) will only be performed when participants are considered clinically fit by the supervising physiotherapist, as CMJ has been demonstrated to be a safe and valid assessment of LL muscle power in community-dwelling older adults [79,80].

Any assessment or exercise session will be immediately interrupted if the participant develops chest pain, severe dyspnea, dizziness, syncope, acute musculoskeletal pain, neurological symptoms, or any other clinical sign judged by the supervising physiotherapist to compromise safe participation. Participants may also stop any assessment or exercise session at their own request.

Adherence to the intervention will be systematically monitored throughout the study period using a structured session-by-session attendance register. A minimum attendance threshold of 80% of scheduled sessions will be required to classify a participant as adherent, consistent with criteria applied in comparable exercise-based trials in older adults. Reasons for any missed session will be documented by the supervising physiotherapist to distinguish between voluntary withdrawal, health-related absence, and logistical barriers, thereby enabling a more nuanced interpretation of adherence patterns across groups and time points.

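### The per-protocol set requires the week-44 visit even for the week-18 contrasts, and its 80% attendance rule has no stated denominator in EXVERBPSY

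*Protocol article*

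**What the plan says.** The primary analysis in section 2.8.1 is intention-to-treat: a constrained longitudinal mixed model that uses every available observation under missing at random. A per-protocol sensitivity analysis is added, restricted to women who attended at least 80% "of scheduled sessions and completed all assessment time points". The time points are T0, T1 (week 18) and T2 (week 44). The five planned contrasts are run at T1 and repeated as a separate family at T2. For the linear trend, T1 is confirmatory and T2 exploratory. Section 2.6.11 states that no supervised sessions take place during follow-up.

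On attendance, section 2.6.1 says "Attendance of ≥80% of scheduled sessions will be considered adequate adherence", and section 2.7.3 says "A minimum attendance threshold of 80% of scheduled sessions will be required to classify a participant as adherent". H4 in section 2.8.1 measures adherence as a single percentage of sessions attended. Section 2.6 schedules "36 supervised multicomponent exercise sessions, and, for one study arm, six structured PSY sessions delivered over 18 weeks", and defines the third arm as "EXVERB plus six structured PSY sessions delivered during the intervention period". None of these places says whether psychoeducation sessions enter the denominator, and none sets a minimum for them. In section 2.8.1, contrasts 4 and 5 are there to "evaluate the incremental contribution of each sequentially added component"; for contrast 4 that component is psychoeducation.

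**The concern.** A per-protocol check at T1 asks what the contrast looks like among women who received the treatment as planned. Whether a woman returns at week 44 says nothing about that, because treatment is over by T1. Requiring the T2 visit removes women who followed the protocol fully and have the T1 measurement. It also selects the T1 sample on an event that happens after the T1 outcome. If return at T2 relates to the T1 result, and does so differently by arm, the check carries a selection that the primary analysis does not have. Such a difference is possible: section 2.6.10 expects psychoeducation to support sustained adherence.

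The attendance rule has a separate weakness. Six psychoeducation sessions are all that separates EXVERBPSY from EXVERB. If the 80% can be met without any of them, the per-protocol version of contrast 4 may include women whose treatment was in effect EXVERB.

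**Working it through.** **Visit rule**

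Inputs: T1 at week 18 and T2 at week 44 (section 2.8.1); 120 randomised, 30 per arm, 20% attrition, 96 analysable (section 2.4).

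1. The plan's own figures agree: 120 × 0.20 = 24 lost, and 120 − 24 = 96.
2. Gap between the visits: 44 − 18 = 26 weeks.
3. Test case: all sessions attended, T0 and T1 completed, T2 missed. Attendance passes, but two of three visits fails the visit condition. She leaves the whole per-protocol analysis, T1 included.
4. Number affected. The article does not say when attrition occurs, so a share s of the 24 is assumed to fall after T1: s = 0.25 gives 6, s = 0.50 gives 12, s = 0.75 gives 18. These are upper figures for each s, because women who also fail the 80% rule would be excluded anyway.
5. Precision, before the attendance rule is applied. With s = 0.50, 120 − 12 = 108 women have T1 data but at most 96 are used. For a simple comparison of means, the standard error grows by √(108/96) = 1.06. For s = 0.25 the factor is √(102/96) = 1.03; for s = 0.75 it is √(114/96) = 1.09.
6. Illustration of selection. If 10% of an arm is removed (3 of 30) and those women lie 0.5 SD below their arm mean at T1 (both assumed), the mean of those who remain rises by 0.10 × 0.5 / 0.90 = 0.056 SD. If the same happens in both arms of a contrast, the shifts cancel. The full 0.056 SD becomes bias only if it happens in one arm.

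**Attendance rule in EXVERBPSY**

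Exercise sessions: 2 per week × 18 weeks = 36, as section 2.6 states. The number needed is 0.80 × scheduled, rounded up.

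| Reading of scheduled sessions | Scheduled | Needed | Woman with 0 of 6 psychoeducation sessions |
|---|---|---|---|
| Exercise only | 36 | 28.8 → 29 | Qualifies from 29/36 = 80.6% |
| Exercise and psychoeducation pooled | 42 | 33.6 → 34 | Qualifies from 34/42 = 81.0%; at most 36/42 = 85.7% |
| Pooled, with four familiarisation sessions (section 2.6.2) | 46 | 36.8 → 37 | Qualifies from 37; at most 40/46 = 87.0% |
| Each component separately | 36 and 6 | 29 and 4.8 → 5 | Fails |

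A woman with no psychoeducation and 29 to 33 exercise sessions qualifies on the exercise-only count and fails on the pooled count (33/42 = 78.6%). The set therefore depends on a choice the article does not make.

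Size of the dilution: if a fraction p of the EXVERBPSY per-protocol set received no psychoeducation, and those women gain nothing from it but are otherwise alike, contrast 4 estimates (1 − p) times the effect of receiving it. In a set of 30, each such woman costs 1/30 = 3.3%. The article gives no basis for guessing how many there would be.

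The same percentage also has a different meaning in the control arm, which has four sessions: 3/4 = 75% fails, so all four are needed.

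**The case against.** The strongest objection is that nothing primary changes. The intention-to-treat model keeps the T0 and T1 data of a woman who misses T2. Multiple imputation and the ANCOVA at T1 and T2 are further pre-specified checks, and neither is said to need complete visits. That stands and limits the point to the per-protocol analysis and the exploratory H4 adherence measure. A reader might infer that the primary T1 result is biased or that women are removed from the trial; the article does not support either.

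A single completer set for a three-visit model is conventional, and any per-protocol set selects on behaviour after randomisation. Both are true. The T2 condition still adds a selection that is irrelevant to treatment received by T1, and the model does not need it.

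A reader might also infer that the article counts a woman with no psychoeducation as adherent. It does not say so. The denominator is undefined, and a per-component reading, which would exclude her, is not ruled out. Detail of this kind is often left to a statistical analysis plan. But the article itself states the 80% rule in three sections and applies it to a two-component arm, so the stated rule is ambiguous. Nor would such women make contrast 4 uninformative: they dilute it, and the case is an extreme one because it requires good exercise attendance.

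Finally, differential loss is a possibility, not something the article implies. Section 2.6.1 promotes adherence generally, and section 2.6.6 uses active pauses for the same purpose in the exercise programme that all three active arms receive.

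**Conclusion.** The visit half holds as a stated rule. The T1 per-protocol contrasts exclude women with adequate attendance and valid T0 and T1 data if they miss T2. Up to about 12 women are affected if half the planned attrition falls after T1 (6 to 18 over the range shown), with a loss of precision of about 3% to 9% on the simple calculation. The 0.056 SD shift is an illustration that rests on assumed values. It is not an estimate of bias in a contrast unless loss differs by arm.

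The attendance half holds as an ambiguity. On two natural counts, a woman with none of the six psychoeducation sessions can qualify, which would weaken a per-protocol reading of EXVERBPSY versus EXVERB by an amount that cannot be estimated from the article. The primary analysis and its conclusions are unaffected. The rule is worth correcting before analysis, because choosing the denominator after seeing attendance would be post hoc.

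**What to change.** - **Section 2.8.1, visits.** Define the per-protocol set by attendance, and set the visit requirement by time point: T0 and T1 for the T1 contrasts, with T2 added for the T2 contrasts. Alternatively, keep all available visits of adherent women in the mixed model.
- **Sections 2.6.1, 2.7.3 and 2.8.1, attendance.** State the 80% rule per component and say whether familiarisation sessions count. With rounding up, this means 29 of 36 exercise sessions and, in EXVERBPSY, also 5 of 6 psychoeducation sessions. Say what the rule means for the four control sessions.
- **Attendance register.** Record exercise and psychoeducation attendance as separate percentages.
- **H4.** Use the exercise percentage as the adherence variable, so that it has the same base of 36 sessions in all three active arms.

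The cost is wording in three sections and one extra register column; treatment, visits and the primary analysis stay as they are. There is one real downside. A psychoeducation requirement makes the EXVERBPSY per-protocol set smaller and selects that arm on a behaviour with no counterpart in EXVERB. The plan should say that the per-protocol version of contrast 4 is to be read with that caution.

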### 2.4. Sample Size Calculation

Sample size was estimated a priori using G*Power 3.1 [37]. Maximal voluntary contraction pressure (mmHg), assessed by manometric perineometry, was selected as the single primary outcome because it provides an objective and quantitative measure of PFM strength and is the outcome most directly related to the primary study hypothesis.

Previous randomized controlled trials involving women with UI have shown that vaginal manometric measures of PFM strength and endurance are responsive to exercise-based interventions incorporating specific or voluntary PFM contractions. In particular, Gonzaga et al. [38] reported improvements in manometric measures of PFM strength and endurance following PFM training and Pilates exercise performed with voluntary PFM contraction in postmenopausal women with UI. However, because previous studies are characterized by relatively small sample sizes and heterogeneous interventions and do not provide either a directly applicable standardized effect size or an established clinically important difference for the planned group-by-time comparison, Cohen’s f = 0.24 was selected as a conservative a priori planning assumption rather than an empirically derived effect estimate [39,40].

The calculation was based on a repeated-measures ANOVA model (within-between interaction; four groups; three time points: T0, T1, T2; two-tailed α = 0.05; statistical power = 1 − β = 0.80; assumed correlation among repeated measures r = 0.50; and Cohen’s f = 0.24). Under these assumptions, the minimum analytical sample required was estimated at 96 participants. Nevertheless, the planned recruitment target was set at 120 participants (30 per group). This target exceeds the minimum sample size required by the formal power calculation and was selected to preserve balanced allocation across the four intervention groups, accommodate anticipated attrition and incomplete follow-up data, and improve the precision and stability of the estimated longitudinal treatment effects obtained from the planned linear mixed-effects models (LMM). The anticipated attrition rate was conservatively estimated at 20%, based on participant retention reported in comparable randomized exercise-based interventions involving older women with UI [7,41,42].

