Aerobic capacity will be evaluated with the Six-Minute Walking Test (6MWT) following standardized guidelines [62]. Gait biomechanics during walking will be assessed using Runscribe^TM^ inertial sensors (Scribe Labs, Moss Beach, CA, USA) placed on both feet, providing spatiotemporal parameters (speed, cadence, stride length, and gait cycle duration for the left and right foot) [63].

E.Lower-Limb muscle power

LL muscle power will be assessed using a Chronojump^®^ contact platform through vertical jumps tests, including the Countermovement Jump (CMJ) and the Abalakov Jump (ABK), which are sensitive to changes in muscular power in older adults [64,65].

LL muscle power will also be evaluated using a Chronojump^®^ linear encoder during two resistance exercises (squat and leg extension). Participants will perform one familiarization repetition followed by two sets of five repetitions for each exercise, with a one-minute rest between sets. All repetitions will be executed with maximal intentional concentric velocity. The Chronojump^®^ system has demonstrated high concurrent validity for displacement and velocity measurements in older adults (r > 0.94) [66]. All assessments will be conducted under standardized safety conditions, including close supervision by trained personnel and the use of protective measures when necessary. Participants presenting pain, dizziness, instability, or any contraindication to maximal effort testing will not perform the corresponding test.

F.Physical function of upper and lower limb

Functional LL performance will be assessed using the Five Times Sit-to-Stand (5tSTS) and the Thirty-Second Sit-to-Stand (30sSTS) tests, both validated and reliable measures of functional strength and physical performance in older adults [61,67,68]. Upper-limb muscle strength will be evaluated using 30 s Arm Curl Test, performed bilaterally, with the number of completed repetitions recorded for each arm [67].

G.Maximal isometric muscle strength

Maximal isometric muscle strength will be assessed using a Chronojump^®^ traction force sensor dynamometer (Chronojump^®^ Boscosystem, Barcelona, Spain), fixed to rigid structures to ensure mechanical stability. Force output will be recorded in newtons (N) and analyzed using the corresponding software (Chronojump^®^ Boscosystem, version 2.3.0-2629-x64).

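### The only missing-data sensitivity analysis named for the primary endpoint (MICE) shares the primary model's missing-at-random assumption, so it cannot test robustness to informative dropout

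*Protocol article*

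**What the plan says.** All the relevant text on analysis is in section 2.8.1 (Data Analysis Plan) of the protocol article.

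- **Primary analysis.** A likelihood-based cLDA model, "which incorporates all available observations under the missing-at-random (MAR) assumption". The section later repeats the limit: "The cLDA model is robust to missing data under the missing-at-random (MAR) assumption and does not require sphericity".
- **Missing-data sensitivity analysis.** "Multiple imputation by chained equations (MICE) will be performed as a pre-specified sensitivity analysis to evaluate the robustness of the primary findings". No imputation model, auxiliary variable, shift, reference-based rule or pattern-mixture term is given.
- **Other checks.** The plan adds a baseline-adjusted comparison: "an ANCOVA model including baseline values as covariates will also be performed for T1 and T2 to evaluate the robustness of the primary cLDA findings". It adds a per-protocol set "including only participants who attended ≥ 80% of scheduled sessions and completed all assessment time points". Little's test is descriptive only, and non-parametric tests are held back for distributional problems.

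On the amount of missing data, section 2.4 says: "The anticipated attrition rate was conservatively estimated at 20" per cent. It does not divide this figure by visit or by arm.

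**The concern.** The assumption most in need of testing is that, given the observed data, women who leave would have fared like those who stay. The analysis named to judge robustness makes the same assumption. If cLDA and MICE agree, the report could present that agreement as reassurance about dropout when it is not.

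The article gives reasons to take informative dropout seriously:

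- Participants cannot be blinded (section 2.5).
- Contact is 36 supervised sessions against four educational ones (Limitations, item i).
- Worse leakage or pelvic pain after exercise is among the adverse events to be recorded (section 2.7.3).
- H4 expects psychological improvement to accompany both better adherence and a larger gain in the primary endpoint. That would be a common driver of staying and responding. It is measured at T1, so it would usually be unobserved in women lost before T1.

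At stake are mainly the three contrasts of an exercise arm with control. If women who are not improving leave the exercise arms, both MAR analyses overstate the benefit by about the same amount, and their agreement hides it.

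**Working it through.** **1. What each named analysis can show about dropout that is not MAR**

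| Analysis (section 2.8.1) | Treatment of missing outcomes | Departs from MAR? |
|---|---|---|
| cLDA | likelihood on all observed data | no |
| MICE | imputed from observed data, no shift stated | no |
| ANCOVA at T1 and T2 | conditions on baseline | no |
| Per-protocol | keeps adherent completers only | no |
| Little's test | examines MCAR, descriptive | no |
| Non-parametric tests | address distribution | no |

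**2. The plan's own attrition figure**

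Inputs from section 2.4: 96 analysable participants, 20% attrition, 120 recruited, 30 per arm.

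96 / (1 − 0.20) = 120, which reproduces the target. If attrition is equal across arms, 30 × 0.80 = 24 per arm are observed. Nothing below depends on how the 96 was obtained.

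**3. Size of the bias**

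Let p be the share missing in an arm at a visit, and δ the number of SDs by which its dropouts are worse than MAR predicts. A MAR analysis overstates that arm's mean by p × δ, so for arm A against arm B:

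bias = p_A × δ_A − p_B × δ_B

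The values of δ are assumptions; the article gives none.

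- Exercise arm against control, p = 0.20, δ = 0 in control: 0.20 × 0.5 = 0.10 SD and 0.20 × 1.0 = 0.20 SD.
- The same with p = 0.10: 0.05 to 0.10 SD.
- Two exercise arms with equal p and δ: 0.20 × 0.5 − 0.20 × 0.5 = 0.
- Two exercise arms, δ = 0.5 in one and 0 in the other: 0.10 SD.

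**4. Relative to the standard error**

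With correlation 0.5 (section 2.4), the baseline-adjusted variance is 1 − 0.5² = 0.75.

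SE = sqrt(2 × 0.75 / 24) = 0.25 SD

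0.10 / 0.25 = 0.4 SE and 0.20 / 0.25 = 0.8 SE.

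The first Holm step over five contrasts is 0.05 / 5 = 0.01, or z ≈ 2.58. An observed z of 2.6 would just pass. Without the bias it would be 2.6 − 0.4 = 2.2 or 2.6 − 0.8 = 1.8, and would fail that step. The 2.6 was chosen near the cutoff to show sensitivity; it is not a prediction.

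**5. Simulation**

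One active arm against control, 30 per arm, T0–T1 correlation 0.5, 20% missing at T1 in each arm, 1,500 runs. The effect is 0.50 SD before any shift. Unobserved T1 values of active-arm dropouts are lowered by δ. ANCOVA on observed data stands in for cLDA. Entries are in SD.

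| δ | Truth, all randomised | MAR likelihood | MAR imputation | Delta-adjusted imputation |
|---|---|---|---|---|
| 0 | 0.500 | 0.508 | 0.508 | 0.508 |
| 0.25 | 0.450 | 0.505 | 0.505 | 0.456 |
| 0.5 | 0.400 | 0.496 | 0.497 | 0.397 |
| 1.0 | 0.300 | 0.503 | 0.503 | 0.305 |

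The two MAR methods agree within 0.001 SD in every row and both stay near 0.50 while the truth falls to 0.30. The last column was given the true δ, so its recovery of the truth is by construction. It shows that the method responds to a departure, not that δ can be learned from the data.

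**The case against.** **An unseen analysis plan may add such an analysis.** This is possible, and the point can only be that none is named here. But the article does more than stay silent: it fixes which analysis will judge robustness, and that analysis cannot see this threat.

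**The article claims nothing false.** This stands. A reader might infer that the plan promises robustness to informative dropout. It does not: it limits the claim for cLDA to MAR and says only that MICE will assess the primary findings.

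**Agreement between cLDA and MICE is not guaranteed.** This also stands. A reader might take the near-identity in the simulation as general, but it used baseline and T1 only. The trial records attendance, reasons for missed sessions and discontinuation, adverse events and co-interventions. Imputation could use these although the stated cLDA fixed effects do not, and MAR might then be more credible. It would still be MAR, so the limit remains.

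**Leaving the exercise programme need not mean a missing outcome.** True. Section 2.6.1 plans outcome collection at each visit whenever feasible, and section 2.7.3 keeps participants with a serious adverse event in the intention-to-treat analysis where feasible. Participants are also not told the hypotheses or what other groups receive (section 2.5). All this may reduce the bias; it does not test for it.

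**The rule on maximal-effort tests is not evidence about the primary endpoint.** Section 2.7.2 says: "Participants presenting pain, dizziness, instability, or any contraindication to maximal effort testing will not perform the corresponding test". A reader might infer health-related missingness in perineometry. The sentence closes the subsection on lower-limb muscle power, which is secondary, and does not support that inference.

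**The scenario is one-sided.** It is. If control dropouts departed from MAR to the same extent, the bias would cancel; if they departed more, its sign would reverse.

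**Conclusion.** The point holds as a limit on what the named check can show. MICE as stated rests on the same MAR assumption as the primary cLDA, and no other named analysis departs from it. Their agreement would say little or nothing about informative dropout, with or without auxiliary variables.

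The illustrative size, an overstatement of 0.10 to 0.20 SD (0.4 to 0.8 SE), applies only to the three active-versus-control contrasts. It requires the full 20% to be missing at the visit analysed, departures of 0.5 to 1.0 SD in the exercise arms, and none in control. The contrasts EXVERBPSY vs EXVERB and EXVERB vs EX are largely protected if dropout and departure are equal, but not if they differ by arm.

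A reader might conclude that the primary result will be biased. The documents do not support that: they give no figure for departures from MAR. The finding is that such bias, if present, would go unseen. It should be corrected because the remedy is cheap; it is no reason to replace the primary model.

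**What to change.** Keep cLDA as primary and keep MICE. Describe MICE as a check under MAR and name any auxiliary variables it will use.

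Add a pre-specified delta-adjusted (tipping-point) analysis of maximal voluntary contraction pressure at T1 and T2:

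- Fix the grid in advance, for example shifts of imputed values from 0 to −1 SD.
- Let the shift vary separately by arm. A common shift in all exercise arms would leave EXVERBPSY vs EXVERB and EXVERB vs EX essentially unchanged at equal dropout, so include settings with one exercise arm shifted relative to the other.
- For each of the five contrasts at each visit, report the shift at which the Holm-adjusted conclusion changes, or state that none in the grid changes it.
- Use the documented reasons for discontinuation to judge which shifts are plausible.

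The cost is a few lines of R on imputations already planned, one extra table, and the need to settle the grid beforehand. Sample size and data collection are unaffected.
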